#### Recruitment {15}

Each investigator center will be responsible for the promotion of the study in the community and for participant recruitment according to eligibility criteria and to regional aspects of population. Investigators may promote the study via social media/TV or other media available, via partnerships with community healthcare services or within the institution’s Hemodynamic Services, Cardiology inpatient and outpatient services. Voluntary patients will also be accepted in the study. In all cases, we will ask investigator sites to fill in a screening log of each approach, including reasons for declining participation, so it will be possible to re-evaluate recruitment strategies throughout the study whenever there is difficulty in achieving recruitment targets.

## Assignment of interventions: allocation

### Sequence generation {16a}

The coordinator center will generate the allocation sequence of 1:1 via validated software with random permuted blocks and stratification, according to the investigator center, to reduce the predictability of a random sequence. Only the study coordination will have access to randomization sequence generation.

### Concealment mechanism {16b}

The allocation concealment mechanism will be central, via website (http://dicanuts.hcor.novatela.com.br).

### Implementation {16c}

The web-based automated randomization system, available 24 h a day, was developed by the IP-HCor. Investigators will need to access the study website, then fill in the electronic CRF and confirm eligibility criteria to be granted access to randomization.

## Assignment of interventions: blinding

### Who will be blinded {17a}

Because of the dietary intervention proposed, this will be an open trial and both participants and care providers will have awareness of dietary approach assigned to each group. Researchers and statisticians will be blinded to the intervention groups during statistical analysis, as well as staff involved with biochemical sample analysis.

### Procedure for unblinding if needed {17b}

This is not applicable. This will be an open-label randomized trial.

## Data collection and management

### Plans for assessment and collection of outcomes {18a}

We will train all researchers (in person or remotely) according to the standard operating manual created for this trial at each investigation site, with special focus on variables that may suffer deviations from inter- and intra-observer variations, such as anthropometric and food consumption measurements.

#### Demographic data

A standardized questionnaire will be administered to all participants for the collection of demographic variables (age, sex, ethnicity, marital status). Socioeconomic and education data will be evaluated according to the Brazilian Criteria for Economics Classification [28].

#### Clinical and lifestyle data

Medical history: Data on type of MI (STEMI or non-STEMI), family history of premature IHD, approximate date of the MI, time of MI diagnosis, history, and approximate date of previous outcomes (i.e., MI before 180 days, stroke, angioplasty with or without stenting, previous CABG) will be collected . Dyslipidemia, hypertension, and diabetes mellitus types 1 and 2 will be registered according to previous reports of medical diagnosis and/or the use of medications to treat each of these conditions.Medications: Data about current drugs in use will be collected. Specifically, regarding use of statins and other lowering lipid drugs, we will ask for type, dosage, and frequency of use.Smoking and alcohol intake: Smoking will be defined as a categorical variable (never, current or past smoking) [29];Excessive alcohol intake will be notified according to sex [30]:
Men: intake of ≥ 30 g of ethanol per day; or ≥ 5 doses in approximately 2 h; or ≥ 5 doses a day of alcoholic beverages in the last month;Women: intake of ≥ 15 g of ethanol per day; or ≥ 4 doses of alcoholic beverages in approximately 2 h; ≥ 5 doses a day of alcoholic beverages in the last month.Physical activity: We will define levels of physical activity as categorical variables according to the International Physical Activity Questionnaire (IPAQ) long version translated and validated into the Portuguese language [31].

#### Anthropometry

Body weight (in kg) should be obtained with participants’ barefoot and wearing minimal clothing. Body height (in cm) should be obtained with participants barefoot in the standing position, and with both arms hanging freely at the side with palms facing thighs. BMI will be calculated, and the nutritional status will be defined according to WHO [32]. Waist circumference and hip circumference (both in cm) should be assessed with a tape measure of resistant, inelastic, and flexible material, with an accuracy of 0.1 cm. Waist circumference will be obtained through the midpoint between the lower edge of the costal arch and the iliac crest in the middle axillary line; the hip circumference will be defined as the measurement with the highest value in the hip region, with the patient’s legs joined. Waist to hip ratio and waist to height ratio will be calculated; abdominal obesity will be classified according to WHO [33] and Ashwell [34] criteria.

#### Biochemical data

Blood samples will be collected, and biochemical assessment will be carried out according to standardized techniques by the clinical analysis laboratories referenced for each center site. TC (mg/dL), HDL-c (mg/dL), TG (mg/dL), FG (mg/dL), FI (mU/L), HbA1c (%), and serum creatinine (Cr, mg/dL) will be obtained directly from blood samples. LDL-c (in mg/dL) will be obtained from Martin’s mathematical formula [35]. VLDL-c (mg/dL), NHDL-c (md/dL), TG/HDL-c ratio (mg/dL), TC/HDL-c ratio (Castelli I index, mg/dL), LDL-c/HDL-c ratio (Castelli II index, mg/dL) and HOMA-IR will be defined according to specific mathematical formulas. Estimated glomerular filtration rate (eGFR, mL/min/1.73 m^2^) will be obtained by mathematical equations specifically for men and women according to the Modification of Diet in Renal Disease Study [36].

#### Dietary assessment

We will use a 24-h dietary recall and a food frequency questionnaire (FFQ) to record data on nutrient intake and eating patterns [37], and both will be applied by trained nutritionists. All data will be recorded in a specific software site (*Sistema Vivanda de Alimentação*®, São Paulo, Brazil) [38]. The same photo album containing images of standardized food portion sizes used in BALANCE Program [11] will be used to assist food intake evaluation.

Diet quality will be evaluated according to the modified Alternative Healthy Eating Index (mAHEI) [39], previously used in the BALANCE trial [12]. Adherence to the dietary prescription will be evaluated according to the BALANCE Index, validated specifically for DICA Br assessment [40].

Each investigation site will be responsible for data collection and transcription into both paper and electronic CRF, at the study website. Variables, procedures, and milestones for data collection are summarized in Table 4.

**Table 4 Tab4:** Data collection plan

Variables	Procedures	Baseline visit	Follow-up week 4	Follow-up week 8	Follow-up week 12	Final assessment week 16
Demographic data (sex, age, ethnicity, marital status); medical history; smoking and alcohol consumption; socioeconomic and educational status.	Questionnaire	x				
Current medications in use	Questionnaire	x	x	x	x	x
*Nutritional assessment and counseling* • Nutrient intake • Energy intake • Healthy patterns and food groups • Diet quality • Diet adherence	24-h dietary recalls and questionnaire	x	x	x	x	x
	FFQ	x				x
	DICA Br counseling	x	x	x	x	x
	mAHEI	x				x
	BALANCE Index	x				x
Physical activity levels	IPAQ	x				X
Anthropometric assessment^a^ (body weight, body height, BMI, waist circumference, hip circumference, waist to hip ratio, waist to height ratio)		x	x	x	x	x
*Biochemical data* • Lipid profile^b^ (TC, HDL-c, LDL-c, NHDL-c, TG, VLDL-c, Castelli indexes I and II, TG/HDL-c); • Glycemic profile^c^ (FG, FI, HbA1c, HOMA-IR); • Kidney function^d^ (Cr, eGRF).	Blood samples	x				x

*FFQ* food frequency questionnaire, *DICA Br DIeta CArdioprotetora Brasileira*, *mAHEI* modified Alternative Healthy Eating Index, *BALANCE* Brazilian Cardioprotective Nutritional Program, *IPAQ* International Physical Activity Questionnaire, *BMI* body mass index, *TC* total cholesterol, *HDL-c* high-density lipoprotein cholesterol, *LDL-c* low-density lipoprotein cholesterol, *NHDL-c* non-HDL cholesterol, *TG* fasting triglycerides, *VLDL-c* very low-density lipoprotein cholesterol, *TG/HDL-c* ratio between TG and HDL-c, *FG* fasting glucose, *FI* fasting insulin, *HbA1c* glycated hemoglobin, *HOMA-IR* homeostasis model assessment-insulin resistance, *Cr* serum creatinine, *eGRF* estimated glomerular filtration rate

^a^General obesity defined as BMI ≥ 30 kg/m^2^ [32]; abdominal obesity defined as waist circumference ≥ 94 cm (men) and ≥ 80 cm (women), waist to hip ratio > 0.90 (men) and > 0.85 (women) [33], and/or waist to height ratio > 0.5 (both sexes) [34]

^b^VLDL-c calculated via formula TG/5; LDL-c calculated via Martin’s formula (LDL-c = TC-HDL-c –TG/X, where X ranges from 3.1 to 11.9 considering TG ≥ 400 mg/dl) [35]; NHDL-c calculated via formula TC – HDL-c; Castelli 1 index calculated via formula TC/HDL-c; Castelli II index calculated via formula LDL-c/HDL-c; TG/HDL-c ratio calculated by dividing TG for HDL-c

^c^HOMA-IR calculated via formula FG (mmol) × FI (UI/mL) ÷ 22.5

^d^eGRF (in mL/min/1.73 m^2^) calculated via formula GRF = 175 × [Cr^−1.154^] × [age^−0.203^] × [0.742, if women] × [1.210, if afro descendant]) [36]

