##### Secondary outcomes

Means of other measures of lipid profile (total cholesterol [TC], high-density lipoprotein cholesterol [HDL-c], very low-density lipoprotein cholesterol [VLDL-c], non-HDL cholesterol [NHDL-c], fasting triglycerides [TG], Castelli indexes I and II, and TG/HDL-c ratio) at 16 weeks;Means of glycemic profile variables (fasting glucose [FG], fasting insulin [FI], glycated hemoglobin [HbA1c], and Homeostases Model Assessment-Insulin Resistance [HOMA-IR]) at 16 weeks;Means of anthropometric measures (body weight, BMI, waist circumference, hip circumference, waist to hip ratio, and waist to height ratio) at 16 weeks.

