## Statistical methods

### Statistical methods for primary and secondary outcomes {20a}

All analyses will follow the intention-to-treat principle. Continuous variables will be presented as means and standard deviations or medians and interquartile range. Categorical variables will be presented as relative and absolute frequencies. The primary outcome will be establishing the difference in LDL-c at 16 weeks after baseline visit between the DICA Br + 30 g of mixed nuts group and the DICA Br. The difference will be assessed with analysis of covariance (ANCOVA) model with LDL-c (16 weeks) as the outcome and treatment group, sites, and baseline LDL-c as covariates. We will also use the ANCOVA on the lipid profile (TC, HDL-c, VLDL-c, NHDL-c, TG, Castelli indexes I and II, and TG/HDL-c ratio) and glycemic profile (FG, FI, HbA1C, and HOMA-IR). Anthropometric measurements that will be collected at baseline, 4, 8, 12, and 16 weeks will be analyzed over the time by generalized estimating equations (GEE) according to the data distribution. For all effect parameters, 95% confidence intervals will be reported. All analyses will consider a two-tailed alpha of 5% and will be performed on the R statistical software.

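### VLDL-c is derived as TG/5 while LDL-c uses TG/X, so the VLDL-c outcome repeats the triglyceride test and does not match the LDL-c derivation; the impact is minor

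*Protocol article*

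**What the plan says.** The protocol article's section on biochemical data says that TC, HDL-c and TG "will be obtained directly from blood samples". LDL-c and VLDL-c are both calculated. Footnote b of Table 4 gives the formulas:

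- VLDL-c: "VLDL-c calculated via formula TG/5", a fixed divisor.
- LDL-c: TC minus HDL-c minus TG/X, "where X ranges from 3.1 to 11.9 considering TG ≥ 400 mg/dl".
- Non-HDL-c: "NHDL-c calculated via formula TC – HDL-c".

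The list of secondary outcomes names VLDL-c and TG as separate items: "very low-density lipoprotein cholesterol [VLDL-c], non-HDL cholesterol [NHDL-c], fasting triglycerides [TG". The statistical methods section (item 20a) gives both the same model: "We will also use the ANCOVA on the lipid profile (TC, HDL-c, VLDL-c, NHDL-c, TG, Castelli indexes I and II, and TG/HDL-c ratio". It adds: "All analyses will consider a two-tailed alpha of 5" per cent. The article gives no reason for using two different divisors.

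**The concern.** In the LDL-c formula, TG/X takes the place of the cholesterol that is neither HDL nor LDL, which is the VLDL-c term. Reporting VLDL-c as TG/5 puts a second estimate of that quantity beside the one already used for the primary outcome. The reported fractions then generally do not add up to total cholesterol, and a reader of the results table could see that non-HDL-c minus LDL-c differs from the reported VLDL-c.

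The fixed divisor also means that VLDL-c carries exactly the information in TG. A chance difference in TG would appear in the table as two agreeing lipid findings. What is at stake is how one secondary outcome is read.

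**Working it through.** **Inputs.** The formulas for VLDL-c, LDL-c and non-HDL-c and the limits of X (3.1 and 11.9) come from footnote b of Table 4. The ANCOVA comes from item 20a. The article gives no TG values and does not say which X applies at which lipid level, so every TG value below, and X of 4 to 6, is an assumption. The plan gives no figure of its own to reproduce here.

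**Step 1: do the fractions add up?**

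HDL-c + LDL-c + VLDL-c − TC
= HDL-c + (TC − HDL-c − TG/X) + TG/5 − TC
= TG(1/5 − 1/X)

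This is zero only if X = 5 (or TG = 0). It is negative for X below 5 and positive for X above 5.

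At an assumed TG of 150 mg/dL, TG/5 = 30.0:

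| X | TG/X (mg/dL) | Gap = 30.0 − TG/X (mg/dL) |
|---|---|---|
| 3.1 (stated limit) | 48.4 | −18.4 |
| 4 (assumed) | 37.5 | −7.5 |
| 5 | 30.0 | 0.0 |
| 6 (assumed) | 25.0 | +5.0 |
| 11.9 (stated limit) | 12.6 | +17.4 |

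The gap scales with TG. At the stated limits of X it is −12.3 to +11.6 mg/dL for TG 100, −24.5 to +23.2 for TG 200 and −36.8 to +34.8 for TG 300. These are outer bounds for an individual, and they suppose that the full range of X can occur at that TG level.

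**Step 2: is the VLDL-c test the TG test?**

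Write the TG model as TG₁₆ = α + τ·group + β·TG₀ + site effects + error. Dividing through by 5 gives

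TG₁₆/5 = α/5 + (τ/5)·group + β·(TG₀/5) + site effects/5 + error/5.

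This is the VLDL-c model. The estimate and its standard error are both divided by 5, so t = (τ/5)/(SE/5) = τ/SE is unchanged, and so is P. If both models used the same baseline covariate instead, such as baseline LDL-c, the result would be the same. After a log transform the constant log 5 goes into the intercept and P is again identical.

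A numerical illustration with simulated data (388 participants, 9 sites; adjusted for baseline and site):

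| Outcome | Difference | SE | 95% CI | t | P |
|---|---|---|---|---|---|
| TG | −7.554 | 6.304 | −19.95 to 4.84 | −1.198 | 0.2315 |
| TG/5 | −1.511 | 1.261 | −3.99 to 0.97 | −1.198 | 0.2315 |

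The simulation only confirms the algebra; it says nothing about what this trial will find. Item 20a names eight secondary lipid outcomes (TC, HDL-c, VLDL-c, non-HDL-c, TG, Castelli I, Castelli II, TG/HDL-c). On observed data, two of the eight tests are the same test.

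**Step 3: what the alternative does.** With VLDL-c = TC − HDL-c − LDL-c = TG/X, the gap is TG/X − TG/X = 0 for every participant. Because X varies, VLDL-c is then no longer a constant multiple of TG. It is, however, exactly non-HDL-c minus LDL-c, and both of those are already analysed.

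**The case against.** The strongest reply is that nothing in the plan depends on this. The article never states or uses the identity TC = HDL-c + LDL-c + VLDL-c. Non-HDL-c and both Castelli indexes are computed without VLDL-c, and the outcome and sample size for the trial's main question rest on LDL-c. Only TG/5 is labelled VLDL-c; TG/X is never reported as an outcome. The secondary list openly contains other overlapping quantities, such as weight and BMI, or TC and HDL-c with non-HDL-c and Castelli I. The TG/5 formula is published, so a careful reader can see the duplication.

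Most of this stands and limits the weight of the point. It does not remove it. The other lipid indices each combine at least two measured quantities, whereas VLDL-c as TG/5 rescales a single listed outcome and cannot disagree with it on observed data.

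Four stronger readings are tempting, and the article does not support them:

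- A reader might take about 18 mg/dL as the expected mismatch. That figure pairs an assumed TG of 150 mg/dL with extremes of X that the article does not assign to that level; as printed, it ties the range to TG of at least 400 mg/dL.
- A reader might infer that one result is formally counted twice. No rule in the article counts agreeing secondary outcomes or claims success on a number of them.
- A reader might say that the VLDL-c implied by the primary endpoint is never analysed. It equals non-HDL-c minus LDL-c, and both are analysed, so its group means can be recovered.
- A reader might extend the problem to the primary outcome. LDL-c uses TG/X only, and TG/5 does not enter it.

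**Conclusion.** The concern holds, as a minor point confined to one secondary outcome. Two statements are exact and follow from the article's own formulas: the reported VLDL-c conflicts with the LDL-c derivation unless X = 5 (or TG = 0), and its ANCOVA on observed data gives the same t and P as the TG ANCOVA. The size of the conflict is not exact. The ranges shown rest on assumed TG values and, for the narrower one, an assumed X of 4 to 6; without the assignment of X by lipid level they cannot be sharpened. The primary LDL-c analysis, its power and its alpha are unaffected, as is non-HDL-c.

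**What to change.** Choose one of two changes and state it before database lock:

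1. Derive VLDL-c as TC − HDL-c − LDL-c, which is TG/X with the same X as for LDL-c. This removes the inconsistency and the identity with TG. State that VLDL-c is then the difference of non-HDL-c and LDL-c, so it is still not an independently measured outcome.
2. Keep TG/5, report VLDL-c descriptively if wanted, and remove it from the separately tested secondary outcomes, with a note that it is TG rescaled and is not evidence beyond TG. This removes the duplicate test but leaves the mismatch with LDL-c, which a table footnote should explain.

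The cost is one line in the derivations or one entry in the outcome list. No new samples, visits or data are needed.

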### Plans to promote participant retention and complete follow-up {18b}

To avoid attrition and maintain stimuli, investigators will be trained to maintain close contact with participants between study appointments, and to remotely collect clinical and dietary data when participants cannot attend the scheduled assessments. Regarding biochemical and anthropometric variables, the participants will be asked about the possibility of having short study visits at their home (following all safety protocols) only for anthropometric measures and blood collection.

### Data management {19}

The objective of our clinical data management plan is to provide high-quality data by adopting standardized procedures to minimize the number of errors and missing data, and consequently, to generate an accurate database for analysis.

Data collection will be performed using electronic CRF via internet at the HCor Data Management System. The system has the following functions: patient registration, 24-h randomization with allocation concealment, data input, data cleaning, and data export for statistical analysis. Data are entered directly into the system by each center. All forms are electronically signed by the principal investigator of each center or by other appointed persons. Instructions for using the system will be made available to investigators.

Several strategies will be performed to generate completeness and correctness of the clinical data. Investigators attended a training session before the start of the study to standardize procedures, including data collection. Study support material will be available at all sites, and the investigators may contact the study coordinating center to solve issues or problems that may arise. Several problems can be detected by the system at the time of data entry. Subsequently, data monitoring will be performed by a data management team in the central office that looks for missing data and inconsistencies using routines implemented in R software.

Monthly, reports of recruitment will be presented for all screened patients by site: the number of days recruiting, number of patients screened and recruited per day, number of screened but not recruited patients, and the reason for non-recruitment. Follow-up data will be assessed, and missing, inconsistent, illogical, out of range, and discrepant data will be marked. Specifically, regarding dietary features, we will screen implausible energy intake according to the criteria: < 500 and > 4000 kcal/day. In addition, 10% of the food recalls will be evaluated in their entirety to confirm all information entered in the electronic CRF and to assess the need for further training. We will notify the investigation sites for corrections or justifications. Resolution of queries by the investigator will be updated in the database. If the investigator cannot provide a resolution, the reasons will be collected in a spreadsheet. The data management team is also responsible for helping to detect cases of protocol deviation. If such situations occur, we will program new training sessions at the site to revise the protocol.

The database will be locked as soon as all data are entered, and all discrepant or missing data are resolved in the database or if all efforts are employed and we consider that the remaining issues cannot be fixed. At this step, our statisticians will review the data before database locking. We will fill out a database lock checklist before locking the database to ensure the completion of activities. After that, the study database will be locked and exported for statistical analysis. At this stage, permission to access the study database will be removed and the database will be archived.

### Confidentiality {27}

We will guarantee confidentiality of data through codified identification of participants (ID) generated by randomization processes, name initials, and birth date. Personal information will not be disseminated and documents containing such information will be confidentially stored and assessed, according to GCP. We will only make the final trial dataset accessible to the allowed investigators.

### Plans for collection, laboratory evaluation, and storage of biological specimens for genetic or molecular analysis in this trial/future use {33}

Storage of blood samples are previewed for this protocol, in preparation for future studies (Supplementary Material, Appendix III).

## Statistical methods

### Statistical methods for primary and secondary outcomes {20a}

All analyses will follow the intention-to-treat principle. Continuous variables will be presented as means and standard deviations or medians and interquartile range. Categorical variables will be presented as relative and absolute frequencies. The primary outcome will be establishing the difference in LDL-c at 16 weeks after baseline visit between the DICA Br + 30 g of mixed nuts group and the DICA Br. The difference will be assessed with analysis of covariance (ANCOVA) model with LDL-c (16 weeks) as the outcome and treatment group, sites, and baseline LDL-c as covariates. We will also use the ANCOVA on the lipid profile (TC, HDL-c, VLDL-c, NHDL-c, TG, Castelli indexes I and II, and TG/HDL-c ratio) and glycemic profile (FG, FI, HbA1C, and HOMA-IR). Anthropometric measurements that will be collected at baseline, 4, 8, 12, and 16 weeks will be analyzed over the time by generalized estimating equations (GEE) according to the data distribution. For all effect parameters, 95% confidence intervals will be reported. All analyses will consider a two-tailed alpha of 5% and will be performed on the R statistical software.

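### Triglycerides, VLDL-c, TG/HDL-c, fasting insulin and HOMA-IR are set as means under ANCOVA in everyone randomised, with no scale stated and no rule for insulin users; this costs power and makes the insulin measures hard to interpret.

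*Protocol article*

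**What the plan says.** Under Secondary outcomes, both families are defined by their averages: "Means of other measures of lipid profile", a list that includes TG, VLDL-c and TG/HDL-c, and "Means of glycemic profile variables (fasting glucose [FG], fasting insulin [FI], glycated hemoglobin [HbA1c], and Homeostases Model Assessment-Insulin Resistance [HOMA-IR]) at 16 weeks".

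Under Statistical methods {20a}, all analyses follow intention to treat. The LDL-c model is an ANCOVA with treatment, site and baseline value. It is then extended: "We will also use the ANCOVA on the lipid profile (TC, HDL-c, VLDL-c, NHDL-c, TG, Castelli indexes I and II, and TG/HDL-c ratio", continuing to "TG/HDL-c ratio) and glycemic profile (FG, FI, HbA1C, and HOMA-IR".

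That section takes account of distribution in two places. For description, "Continuous variables will be presented as means and standard deviations or medians and interquartile range". For inference, the anthropometric measures "will be analyzed over the time by generalized estimating equations (GEE) according to the data distribution". Neither covers the ANCOVA outcomes.

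On the population, the eligibility criteria {10} exclude neither diabetes nor insulin treatment, and under Clinical and lifestyle data "Dyslipidemia, hypertension, and diabetes mellitus types 1 and 2 will be registered". Current drugs are recorded at baseline and at every later visit (Table 4). The footnotes to Table 4 compute HOMA-IR as fasting glucose times fasting insulin divided by 22.5, and VLDL-c as TG/5. No restriction for insulin users is stated anywhere.

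**The concern.** There are two separate issues.

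**Scale.** TG and fasting insulin are concentrations bounded below by zero, TG/HDL-c is a ratio and HOMA-IR is a product. Such variables tend to be right-skewed, and treatment effects on them are often closer to proportional than additive. A comparison of arithmetic means then gives a few high values much of the weight, and the confidence interval widens.

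**Population.** HOMA-IR is informative only if fasting insulin reflects the participant's own secretion in response to glucose. In someone who injects insulin, the measured value may include the injected dose, and the participant's own secretion may be absent (type 1) or altered. The number no longer indexes insulin resistance on any scale. Averaging these participants in with the rest blurs both fasting insulin and HOMA-IR.

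At stake are the precision of five secondary outcomes and the meaning of two of them.

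**Working it through.** **The plan's own figure.** The only design calculation is for LDL-c: SD 24, baseline correlation 0.6, difference 6 mg/dL, 80% power, two-sided 5%, 352 evaluable. With n per arm = 2 × (1.960 + 0.842)² × SD² × (1 − r²) / difference², r = 0.6 gives 2 × 7.849 × 576 × 0.64 / 36 = 160.7, so 161 per arm and 322 in total. An r of 0.55, which rounds to 0.6, gives 176 per arm, or 352. The printed figure is therefore explained by rounding and errs on the safe side. It has no bearing on this point. No power is given for any secondary outcome, so only n and r are borrowed below.

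**Inputs for the scale question**
- From the document: 176 evaluable per arm; two-sided alpha 5%.
- Borrowed from LDL-c: r = 0.6, here ASSUMED on the log scale for the other variables.
- ASSUMED, because the document gives nothing: log-normal outcomes, log-SD between 0.4 and 1.0, and a proportional effect.

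**Effect size.** It is set so that log-scale ANCOVA has 80% power:

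log ratio = −(1.960 + 0.842) × log-SD × √(1 − 0.6²) × √(2/176)

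At log-SD 0.5 this is −2.802 × 0.5 × 0.8 × 0.1066 = −0.119, a ratio of 0.887. At log-SD 0.7 it is −0.167, a ratio of 0.846.

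**Result.** Simulated trials, baseline-adjusted ANCOVA, site effects left out for simplicity; 10,000 trials per setting, except that the row at 0.7 comes from separate runs at about the same sample size:

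| log-SD | ratio | log-scale power | original-scale power |
|---|---|---|---|
| 0.4 | 0.909 | 80% | 75% |
| 0.5 | 0.887 | 80% | 72–73% |
| 0.6 | 0.866 | 79% | 68% |
| 0.7 | 0.846 | about 80% | about 66% |
| 0.8 | 0.826 | 80% | 62% |
| 1.0 | 0.787 | 80% | 52% |

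With no true effect, the original-scale analysis rejected in 4.7% to 5.3% of trials for log-SD 0.4 to 1.0.

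**In terms of participants.** The effective fraction of the sample is ((z of achieved power + 1.960) / 2.802)². At 72% power it is (0.583 + 1.960)² / 7.849 = 0.82. At 66% it is (0.412 + 1.960)² / 7.849 = 0.72. Under these assumptions, original-scale analysis is like losing about 18% to 28% of participants.

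**Insulin users.** The document gives neither their share nor their insulin values, so this is an illustration only. ASSUMED: users' values doubled, extra visit-to-visit log noise with SD 0.8, no treatment effect in users, log-SD 0.5 to 0.7 otherwise.

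| share of users | original scale, everyone | log scale, everyone | log scale, non-users only |
|---|---|---|---|
| 5% | 30–34% | 63–69% | about 77% |
| 10% | 18–23% | 51–60% | about 76% |

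Type I error with 5% users was about 4%. The log scale alone recovers only part of the loss; restricting the population recovers most of the rest.

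**VLDL-c.** Because it is TG/5, log VLDL-c is log TG minus a constant. The two give the same test on either scale, so they must be handled alike.

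**The case against.** The strongest reply is that much of this is inferred from silence. The article does not use the word raw or untransformed, and an ANCOVA on logged data is still an ANCOVA. It condenses a fuller protocol, and the statistical analysis plan, where transformations are commonly settled, is not shown. A reader might infer that the trial has committed itself to untransformed analysis; the text does not go that far. What stands is that the article fixes means as the outcomes and confines its distribution clause to the anthropometric GEE. A log-scale analysis elsewhere would estimate ratios of geometric means, a different quantity from the one defined here, and the two would have to be aligned.

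Second, a difference in means is a valid target, and its type I error holds. This stands: the argument is about efficiency and meaning, not validity. The power figures also come from the setting that most favours logs, with exact log-normality and a proportional effect. The direction is credible; the size is conditional.

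Third, the document names no insulin assay, so how far injected insulin registers is unknown. This also stands, and it is why no size can be fixed. It does not rescue the measure, because a reading that misses injected insulin still does not describe insulin resistance in that participant.

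Fourth, subgroups by previous comorbidities are planned and might include diabetes. They would not repair the overall fasting insulin and HOMA-IR estimates.

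A reader might also infer that an imbalance in insulin users could produce a false treatment effect. Randomisation within centre leaves only chance imbalance, which the nominal 5% error rate already covers.

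**Conclusion.** The point holds in a limited form. As written, TG, VLDL-c, TG/HDL-c, fasting insulin and HOMA-IR are means compared by ANCOVA in everyone randomised, with no transformation named and no provision for insulin users in a population that admits both types of diabetes.

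Under right skew the price is power: about 66% to 72% instead of 80%, if the data are log-normal with log-SD 0.5 to 0.7, the log-scale correlation is 0.6 and the effect is proportional. None of these conditions can be confirmed from the document. The fasting insulin and HOMA-IR estimates are also hard to interpret to the extent that insulin users are enrolled, and that extent is not stated.

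The documents do not support a claim of inflated false positives or of an invalid analysis. The LDL-c primary analysis and the sample size are unaffected. This is a worthwhile improvement to secondary outcomes.

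**What to change.** Before database lock, and without reference to results by arm, state the following in the analysis plan and align the Secondary outcomes definition with it.

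1. Analyse TG, VLDL-c, TG/HDL-c, fasting insulin and HOMA-IR by the same ANCOVA on the log scale, with log baseline value and site as covariates. Report ratios of geometric means with 95% confidence intervals. Note that VLDL-c, being TG/5, repeats the TG test.
2. Analyse fasting insulin and HOMA-IR primarily in participants not using insulin at baseline, identified from the medication record. Report the all-participant result as sensitivity analysis. Because the subset is fixed by a baseline characteristic, the randomised comparison is preserved. Insulin started after randomisation should not remove anyone from it.

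If the full analysis plan already does this, only the outcome definitions need aligning. No new data are required. The cost is wording, effects expressed as ratios instead of differences in original units, and a slightly smaller n for fasting insulin and HOMA-IR.
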